### Participant timeline {13}

Person is identified as eligible.

↓

Discussion regarding study with clinician or member of the research team.

(after discussion with clinician).

Participant information sheet and consent form provided.

↓

Examination that assesses ARM feasible.

(either at presentation or after cervical preparation for induction of labour).

*People who go into labour from cervical preparation who no longer require oxytocin or with people who undergo SRM prior to randomisation are screen fails and are not randomised.

↓

Randomisation (online randomisation system [17]).

↓

IOL commences.

(*Early ARM group*: oxytocin infusion started and ARM within 60 min).

(*Late ARM group*: oxytocin started and ARM at 6 cm or more cervical dilation or at 12 h of oxytocin infusion).

↓

Participant completes post-induction survey regarding their birth experience.

↓

Data collection baseline demographics, labour and birth, maternal outcomes and neonatal outcomes to discharge from hospital.

### SPIRIT figure

[figure not shown]

### Sample size {14}

A power calculation has been performed utilising the OpenEpi (https://openepi.com) program comparing the rates of chorioamnionitis between groups. The power calculation is based on the findings from the existing literature indicating a decrease in indicators of maternal infection when ‘Late ARM’ is performed [8, 9]. In order to show a decrease in chorioamnionitis from 9 to 3%, with power set at 80% and a 95% CI, 244 participants per arm are required, or 488 participants in total. The goal is to recruit 500 participants to this trial to account for participant withdrawals of data or loss to follow-up. The additional 12 participants are thought to be sufficient for the purposes of this trial as it would be highly unusual for a labouring patient to be ‘lost to follow-up’ for the primary outcome (which occurs in labour). We anticipate that the choice to withdraw data from analysis will be uncommon.

### Recruitment {15}

All eligible people and their care providers can access information about the study on the trial website ARM.auckland.ac.nz. Trial information sheets and trial pamphlets are available to potential participants when they present for induction as well as through the hospital clinics. There are research employees available to recruit for the trial through the assessment unit at the Auckland City Hospital. Participants have an in-person discussion regarding the trial with a member of staff or a member of the study team. At this time, they are provided with a participant information sheet and consent form to read. They are given time to review the materials and then may elect to participate. Written informed consent is required for participation.

## Assignment of interventions: allocation

### Sequence generation {16a}

Randomisation occurs via the Liggins institute Clinical Data Research Hub [17]. This service provides an electronic tool for participant screening and randomisation. The site contains a password-protected login, and the screening questions must indicate eligibility for the person to be randomised. Each patient identification number can only be randomised once within a 9-month period; hence, the randomisation cannot be performed more than once during the same pregnancy.

### Concealment mechanism {16b}

While there is allocation concealment until the point of the trial intervention being performed, blinding of participants and clinicians and data extractors is not feasible for this study. Data analysis will be blinded to study allocation.

### Implementation {16c}

The randomisation is computer generated and outsourced to the Liggins Institute Clinical Data Research Hub. The research midwives and investigators who enrol participants do not have access to the randomisation schedule. People can consent to the study at admission to the hospital for induction of labour. At Te Toka Tumai Auckland, IOL patients are initially seen in the Women’s Assessment Unit and cervical preparation undertaken in that location. When they are found to have a favourable cervical examination, they await transfer to delivery unit.

Once a participant arrives on delivery unit and is ready to commence induction with oxytocin, the midwife caring for the participant on delivery unit accesses the computerised randomisation site. The study intervention is then assigned electronically.

#### Screen failures

Participants in the study will frequently consent to inclusion either prior to or during cervical preparation for induction. Participants who have provided informed consent to be randomised who go on to labour with cervical preparation alone (thereby not requiring oxytocin infusion) or who undergo SRM (spontaneous rupture of membranes) prior to transfer to delivery unit are treated as ‘screen failures’ and are not randomised. While this may potentially result in a high rate of ‘screen failures’, the study was designed to have randomisation only once on the delivery unit thereby avoiding differential treatment of participants prior to oxytocin commencement based on study arm.

## Assignment of interventions: blinding

### Who will be blinded {17a}

It is not feasible to blind clinicians or participants to the study intervention. The statistician will be blinded to the study intervention during the analysis.

### Procedure for unblinding if needed {17b}

N/A. This study is not blinded.

### Data collection and management

#### Plans for assessment and collection of outcomes {18a}

Baseline data collection is from chart extraction.

Trial data collection is from chart extraction. Research employees performing chart extraction receive in-person training. Data collection is via electronic chart review. In relation to the primary outcome, vitals are reliably charted and the provision of antibiotics only occurs with a written record of the drug order. The secondary outcomes are all part of the standard data entry for all births (including for people not enrolled in the study) on our unit. Survey data is only completed either in person or via phone and is not available from the participant record.

Data is entered into a secure dataset.

#### Plans to promote participant retention and complete follow-up {18b}

There is 100% follow-up rate for participants for their immediate labour outcomes, as they remain on the unit for all study procedures. If any data is not able to be located within the chart, this data will be reported as missing for that individual outcome and not imputed. There is follow-up for a post-birth survey. This may be performed in person at a clinical encounter related to birth care (hospital or clinics) but is usually performed via phone. Attempts at contact are made three times via phone call for the post-birth survey.

#### Data management {19}

Data is entered into a secure dataset with identifiers removed. The dataset is accessible only to research staff. A separate list of participants is kept, only available to research staff.

#### Confidentiality {27}

Data is stored in a manner that has identifiers removed. The dataset of participants is kept on a secure server which is only accessible by study staff. All outputs from this research will be presented in an aggregated manner in a way that individual participants would not reasonably be able to be identified.

#### Plans for collection, laboratory evaluation and storage of biological specimens for genetic or molecular analysis in this trial/future use {33}

N/A. There are no biological specimens being collected as a part of this study.

## Statistical methods

### Statistical methods for primary and secondary outcomes {20a}

Descriptive data will be presented on the study groups.

Analyses will follow the principle of intention-to-treat. Missing data will not be imputed and will be presented as missing for these variables.

Additionally, a per-protocol analysis will also be undertaken, which will exclude from analysis any participant in the ‘Early’ ARM group who had ARM performed greater than 60 min after commencement of oxytocin infusion and any participant from the ‘Late’ ARM group who had ARM performed before 6 cm dilation or 12 h from oxytocin commencement due to trial procedure withdrawal. Participants who have protocol deviations for clinical indications (for example to place a fetal scalp electrode due to fetal heart rate abnormalities) will remain in the analysis.

Primary and secondary outcome analyses will be adjusted for the stratification variable using regression techniques, and outcomes presented as relative risks or mean differences with 95% confidence intervals.

A *p* value of 0.05 will be considered statistically significant. There are multiple secondary outcomes. These will be reported with *p* values without adjustment for multiplicity but recognised as exploratory.

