### Intervention description {11a}

Amniotomy is a common obstetric procedure during which a gloved hand is used to perform a vaginal examination. Once the cervix is located and the examiner’s fingers are placed inside the dilated portion, against the amniotic membrane, a plastic amnihook is advanced along the fingers. The instrument has a sharp ‘hook’ at the end. This end of the implement is utilised to cause a small tear in the amniotic membrane, after which time some of the amniotic fluid is usually felt to be expelled vaginally.‘Early ARM’ group: ARM is performed either prior to or within 60 min of commencement of oxytocin infusion‘Late ARM’ group: oxytocin infusion is commenced first, and ARM is performed at ≥ 6 cm cervical dilation or if the participant has been receiving oxytocin infusion for at least 12 h and has not yet reached 6 cm of cervical dilation

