Lastly, it has been noted that there have been several protocol violations in the ‘Late ARM’ group in the trial. This is for a variety of reasons, including misunderstanding of the trial protocol, participant request for amniotomy or staff obstetrician/LMC recommendation for amniotomy without a clear indication for this to be performed. This is not entirely unexpected, considering the strong belief amongst some care providers that amniotomy is important to induction of labour and the ability of participants to withdraw from the study at any time. Now that the trial is well underway and there has been ongoing unit and individual education about the trial, most people are treated per trial allocation. The investigators will perform a per-protocol analysis when recruitment is complete and the rate of protocol violations for both participant and caregiver-driven reasons is known.

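### The per-protocol rule does not cover the staff-driven Late-arm violations that the article itself reports, so read literally those non-adherent participants stay in the per-protocol set

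*Protocol article*

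**What the plan says.** In Statistical methods {20a} of the protocol article, the governing principle is "Analyses will follow the principle of intention-to-treat". A per-protocol analysis comes in addition. It excludes:

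- Early participants "who had ARM performed greater than 60 min after commencement of oxytocin infusion";
- Late participants "who had ARM performed before 6 cm dilation or 12 h from oxytocin commencement due to trial procedure withdrawal".

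The words that set the limit are "from oxytocin commencement due to trial procedure withdrawal".

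The following sentence says who is kept: "Participants who have protocol deviations for clinical indications (for example to place a fetal scalp electrode due to fetal heart rate abnormalities) will remain in". In other words, such participants are not excluded.

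Intervention description {11a} defines Late timing by two alternatives: reaching the dilation mark, or not having reached it when the participant "has been receiving oxytocin infusion for at least" 12 h.

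Criteria for discontinuing or modifying {11b} presents withdrawal from procedures as something the participant does, with a request for Early ARM as its example.

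The Discussion says that several Late-arm violations have occurred. It lists misunderstanding of the trial protocol and "participant request for amniotomy or staff obstetrician/LMC recommendation for amniotomy without a clear indication for this to be performed". It adds: "The investigators will perform a per-protocol analysis when recruitment is complete and the rate of protocol violations" is known for both participant-driven and caregiver-driven reasons.

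**The concern.** The rule in {20a} sorts Late-arm deviations by reason and names two: withdrawal (out) and clinical indication (in). The Discussion names three causes of violation, and only participant request falls under either heading. Misunderstanding of the protocol falls under neither. Nor does staff advice without a clear indication.

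Because the rule is written as a list of exclusions, anyone not listed stays in. The Late per-protocol set would then contain people who had ARM too soon with no clinical reason, which is the group such an analysis exists to remove. The Discussion shows that the investigators expect non-adherence and mean to use this analysis to address it, so readers will look to it. A programmer applying the text would keep these participants; an investigator applying the apparent intent might drop them. That choice should not be open once outcomes are visible.

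**Working it through.** **Matching reasons to the rule**

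| Reason for ARM too soon in Late | Source | Treatment under {20a} |
|---|---|---|
| Participant request | Discussion; example of withdrawal in {11b} | Excluded |
| Clinical indication, such as a scalp electrode | {11b}, {20a} | Kept, on purpose |
| Misunderstanding of the protocol | Discussion | Not named, so kept |
| Staff advice without clear indication | Discussion | Not named, so kept |

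**Planning rates.** Sample size {14} gives 9% Early and 3% Late with 244 per arm. The pooled normal formula at two-sided 5% and 80% power gives (1.960·√(2·0.06·0.94) + 0.842·√(0.09·0.91 + 0.03·0.97))² / 0.06² = 244.75. This agrees with the stated 244 to within rounding, so 9% and 3% are used below.

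**Size of the dilution (illustrative).** Assumptions, none from the documents:

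- 15% of Late participants have ARM before either Late criterion is met.
- The reasons split equally: 5% withdrawal, 5% staff-driven (misunderstanding or advice), 5% clinical.
- These participants carry the Early risk of 9%, and adherent Late participants carry 3%.
- Every Early participant adheres.

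With violation share v and retained violator share r, Late risk = [(1 − v)·3% + r·9%] / [(1 − v) + r]. The arm size of 250 is half the recruitment target of 500.

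| Late set | r | Calculation | Late risk | RR against 9% | n of 250 |
|---|---|---|---|---|---|
| Intention-to-treat | 0.15 | 2.55 + 1.35 | 3.90% | 0.43 | 250 |
| {20a} read literally | 0.10 | (2.55 + 0.90)/0.95 | 3.63% | 0.40 | 237.5 |
| Staff-driven also excluded | 0.05 | (2.55 + 0.45)/0.90 | 3.33% | 0.37 | 225 |
| All deviations excluded | 0 | 2.55/0.85 | 3.00% | 0.33 | 212.5 |

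The gap belonging to the unclassified group is the second row against the third: 3.63% against 3.33%. The remaining step to 3.00% comes from the clinical deviations, which the plan keeps openly.

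**Range (literal rule against staff-driven also excluded, equal split):**

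- v = 5%: (2.85 + 0.30)/0.983 = 3.20% against (2.85 + 0.15)/0.967 = 3.10%; RR 0.36 against 0.34.
- v = 20%: 3.86% against 3.46%; RR 0.43 against 0.38.
- v = 30%: (2.10 + 1.80)/0.90 = 4.33% against (2.10 + 0.90)/0.80 = 3.75%; RR 0.48 against 0.42.

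If all of a 15% violation share were staff-driven, the literal rule would exclude nobody: 3.90% against 3.00%, RR 0.43 against 0.33.

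**The case against.** The best case for the plan is that this is a supplementary analysis, that sorting deviation reasons is ordinary content for an analysis plan not shown here, and that the Discussion shows awareness of caregiver-driven violations. The first part stands and limits the severity. The second does not dispose of the point: {20a} states an explicit rule, and the same article reports violations that the rule does not cover. Awareness in the Discussion does not say whether those participants are in or out.

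Several stronger readings are tempting but not supported:

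- *The wording about 6 cm or 12 h would exclude compliant participants.* In ordinary use it means before either milestone, which matches {11a}. A compliant ARM is also not due to withdrawal, so the clause cannot remove it. Clearer wording would help, but this is not an error.
- *The two arms have different rules.* This depends on attaching the withdrawal phrase to the Late clause alone. It closes a sentence covering both arms and can govern both. On that reading the asymmetry disappears, while staff-driven deviations remain unclassified in both arms.
- *Staff-driven violations are the main ones.* No counts are given, and the Discussion says most people are now treated as allocated.
- *The rule manufactures a benefit by removing poor-prognosis Late participants.* Selection on post-randomisation events affects any per-protocol analysis, and its size here rests wholly on assumption. Suppose there is no true effect, 20% of participants have slow labour with 20% risk, and the others have (9 − 0.2·20)/0.8 = 6.25%. Excluding 5% of the Late arm, all of them slow labours, gives (0.15·20 + 0.80·6.25)/0.95 = 8.42%, RR 0.94. That justifies a cautious label, not a finding of bias.

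**Conclusion.** The point holds in a limited form. As written, the per-protocol rule leaves in the Late set participants who had ARM too soon through misunderstanding or unindicated staff advice, and the article reports that both occur. On the stated assumptions this moves the Late risk from 3.3% to 3.6% and the relative risk from 0.37 to 0.40. The shift grows with the violation rate and the staff-driven share, neither of which is reported. It is a modest dilution towards no effect in a supportive analysis.

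A reader might infer that the trial's main conclusion is at risk. It is not: the primary analysis is by intention-to-treat and does not use this rule. The correction is still worth making, because it is cheap and removes a choice that could otherwise be made after results are seen.

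**What to change.** Before data lock and blind to outcomes, reword {20a} and carry the same text into the statistical analysis plan:

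1. **One rule for both arms.** Exclude any participant whose ARM timing departed from the {11a} definition of the allocated arm for any reason other than a clinical indication, whether prompted by the participant or by staff. For Late, a departure is ARM when neither the dilation criterion nor the time criterion in {11a} had been met.
2. **Sensitivity analysis.** Repeat the analysis with the clinically indicated deviations also excluded.
3. **Label.** Call the per-protocol result supportive, because it selects on events after randomisation.

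A complier-average analysis is optional. If used, its exposure must capture every Late-arm ARM before the {11a} criteria. An exposure defined only as ARM within 60 min of oxytocin start would code a violation at, say, 3 h as adherent.

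The cost is a revised sentence, one extra run and a slightly smaller set (in the illustration, 225 instead of 237.5 of 250 Late participants). ARM time, dilation, oxytocin start and the reason for deviation are already needed to apply the present rule.

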The first trial, involving 209 participants in the United States, identified a marked difference in people undergoing amniotomy in rates of chorioamnionitis (22.6% versus 6.8%, *p* = 0.002 in the early ARM versus late ARM groups, respectively) and variable decelerations (19.6% versus 6.4%, *p* = 0.08 in the early ARM versus later ARM groups, respectively) [8]. The second trial including 168 people recruited in Israel identified an elevated risk of intrapartum fever (which we consider to be a surrogate for chorioamnionitis) in the early ARM group (8.7% versus 2.3%, RR 1.69; 95% CI 1.15–2.5) in addition to a higher risk of caesarean birth in the early ARM group (25% versus 7.9%, RR 1.74; 95% CI 1.30–2.34) [9]. Lastly, a trial from India in which 150 women were randomised indicated shorter labours (7.35 h versus 11.66 h, *p* = 0.000) but a significant increase in caesarean rate (2.7% versus 10.7%, *p* = 0.049) when ARM was performed early [10].

A further two trials indicated that early and late amniotomy yielded equivalent outcomes between groups for rates of infection [11, 12]. The first of these trials was carried out in Canada and was unfortunately closed to recruitment at 143 participants after 3 years because of the low recruitment rate [11]. The primary outcome was rate of caesarean birth, which did not differ for nulliparous (18 vs 17%, *p* = 0.91) or parous (0 vs 3%, *p* = 1.0) people in the early and late amniotomy groups, respectively. This trial also indicated a non-significant trend towards fewer fevers in the early amniotomy group (3 vs 25%, *p* = 0.05). The second of these trials was performed in the United States and included 585 participants, all of them nulliparous [12]. The primary outcomes of the trial were time from induction to birth (19.0 vs 21.3 h, *p* = 0.04) and percentage of people who gave birth within 24 h (68 vs 56, *p* = 0.002) in the early and the late amniotomy groups, respectively. Chorioamnionitis rates were equivalent between groups (11.5 vs 8.5%, *p* = 0.22). However, in this trial, most people in the early ARM group had ARM at 3 cm cervical dilation, making the trial incomparable to the New Zealand context, where amniotomy is frequently performed as soon as feasible, which is at a cervical dilation that permits the insertion of an amniohook instrument (often 1–2 cm of dilation).

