### Trial design {8}

The ARM trial is a randomised controlled trial being performed at a single institution in New Zealand, Te Toka Tumai Auckland. Participants undergoing oxytocin IOL are randomised to either ‘Early ARM’ or ‘Late ARM’ in a one-to-one ratio, stratified by parity (parity = 0 or ≥ 1). The primary hypothesis is that people undergoing ‘Late ARM’ will have a lower chance of developing chorioamnionitis than those people undergoing ‘Early ARM’.

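### Adjusting for parity alone is valid, but adding cervical dilation from the pre-randomisation examination would give a modest, low-cost gain in precision on the labour-duration outcomes

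*Protocol article*

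**What the plan says.** In the protocol article, Statistical methods for primary and secondary outcomes {20a} says: "Primary and secondary outcome analyses will be adjusted for the stratification variable using regression techniques". Trial design {8} identifies that variable: randomisation is "stratified by parity (parity = 0 or ≥ 1"). Results are to be given as relative risks or mean differences with 95% confidence intervals, and the secondary outcomes are declared exploratory.

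Participant timeline {13} lists, ahead of the randomisation step, "Examination that assesses ARM feasible", done "either at presentation or after cervical preparation for induction of labour". Implementation {16c} adds: "When they are found to have a favourable cervical examination, they await transfer to delivery unit". Randomisation then takes place on the delivery unit. Under Plans for assessment and collection of outcomes {18a}, "Baseline data collection is from chart extraction"; the article does not list the baseline variables.

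In Background and rationale {6a}, the 585-participant trial, the largest of the five cited, is set aside because "most people in the early ARM group had ARM at 3 cm cervical dilation, making the trial incomparable to the New Zealand context". Local amniotomy is described as often done at 1–2 cm.

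**The concern.** How dilated the cervix is when oxytocin starts plausibly bears on how long the induction takes. In the Late arm it also fixes how far a participant is from the 6 cm trigger. Parity captures only part of this. A prognostic value measured before randomisation can be added to a model without biasing the comparison. It removes residual variance and corrects chance imbalance that stratifying on parity alone does not control. If dilation is prognostic, models without it give wider intervals than the same data could support.

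What is at stake is precision on secondary outcomes, mainly time from oxytocin to vaginal birth and time from membrane rupture to vaginal birth (outcomes 14 and 15). The validity of the trial and the primary comparison are not at stake.

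**Working it through.** **Inputs from the article.** Chorioamnionitis 9% versus 3%, 80% power, 95% CI, 244 per arm and 488 in total (Sample size {14}); 1:1 allocation and the parity strata (Trial design {8}); relative risks or mean differences ({20a}); outcomes 14 and 15 measured to vaginal birth and presented as medians (Outcomes {12}).

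**Not in the article.** Any association between baseline dilation and an outcome. Every gain below is therefore a range over stated assumptions.

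**1. The plan's own figure.** Two proportions, two-sided 5%, no continuity correction:

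n = [1.960·√(2·0.06·0.94) + 0.842·√(0.09·0.91 + 0.03·0.97)]² / 0.06² = (0.658 + 0.280)² / 0.0036 ≈ 244.7, so 245 per arm.

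This agrees with the stated 244 up to rounding. Power at 244 per arm is 79.9%. Expected primary events are 244 × (0.09 + 0.03) ≈ 29. Nothing below changes the sample size.

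**2. Duration, as a mean difference.** If dilation explains a share R² of the variance left after parity, the standard error is multiplied by √(1 − R²), and the gain in equivalent participants is 1/(1 − R²) − 1.

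| Assumed partial R² | SE multiplier | SE reduction | Equivalent gain | 488 acts like |
|---|---|---|---|---|
| 0.02 | 0.990 | 1.0% | 2.0% | 498 |
| 0.05 | 0.975 | 2.5% | 5.3% | 514 |
| 0.10 | 0.949 | 5.1% | 11.1% | 542 |
| 0.20 | 0.894 | 10.6% | 25.0% | 610 |

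The last column treats all 488 as contributing, but outcomes 14 and 15 exist only for vaginal births. With an assumed 20% caesarean rate, about 0.8 × 488 = 390 contribute. The 390 would act like 390/0.98 = 398 at the low end and 390/0.80 = 488 at the high end. The percentages are unchanged, but the head count is smaller. The formula is for means and gives no figure for a difference in medians.

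**3. Caesarean, as a relative risk.** Simulation with N = 488, 500 runs per scenario and robust Poisson regression, comparing parity only with parity plus dilation. Assumptions: early-arm rate 20% or 25%; relative risk 0.6; 40% parous with odds ratio 0.3; dilation centred on 2.5 cm with SD 1, limited to 1–5 cm.

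| Assumed odds ratio per cm | SE ratio at 20% | SE ratio at 25% | SE reduction |
|---|---|---|---|
| 0.80 | 0.997 | 0.997 | 0.3% |
| 0.65 | 0.990 | 0.989 | about 1% |
| 0.50 | 0.977 | 0.974 | about 2.5% |

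The largest change in power was 1.4 points (78.8% to 80.2%).

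**4. Chorioamnionitis, 9% versus 3%.** Under the same set-up the SE ratios were 0.999, 0.997 and 0.991, a reduction of 0.1% to 0.9%. Power moved in both directions (80.0% to 80.6%, 79.2% to 80.8%, 81.0% to 80.4%), so it is essentially unchanged.

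**The case against.** The strongest reply is that nothing here is wrong. Adjusting for the stratification factor matches the randomisation and is a valid analysis, and a further covariate is a choice about efficiency. The statistical analysis plan is not shown and might already name one. Both points stand as limits on severity. They do not remove the suggestion, because {20a} positively states what the models adjust for and does not leave it open.

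Several stronger readings are tempting and are not supported:

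- A reader might infer that dilation is measured just before randomisation. The examination may be at presentation or after cervical preparation, and a wait for transfer follows. The value can be somewhat old and of varying age. It remains a valid baseline covariate, but its predictive strength may be lower.
- A reader might take the phrase "making the trial incomparable to the New Zealand context" as the article's own evidence that baseline dilation is prognostic. That passage concerns dilation at amniotomy and comparability with local practice. It says nothing about prediction within this trial.
- A reader might infer that appreciable precision is being lost on caesarean or on the primary outcome. The working shows very little for the first and almost nothing for the second.
- A reader might infer that the trial will not report dilation by arm. The article promises descriptive data without listing the variables, which is ordinary condensation.

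It is also fair to say that entry dilation may span a narrow range, since participants must still need oxytocin. That would favour the low end of the R² range. Finally, {20a} says missing data will not be imputed, so filling a missing dilation value needs an explicit clause.

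**Conclusion.** The point holds as a modest improvement. Parity-only adjustment is valid as it stands. Adding pre-randomisation dilation would reduce the standard error of a mean difference in duration by about 1% to 11%, among vaginal births, for an assumed partial R² of 0.02 to 0.20. For caesarean relative risks the reduction is about 0.3% to 2.5%, and for chorioamnionitis at most 0.9%.

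These figures rest on assumed associations, on dilation in centimetres being charted at the examination, and on duration being compared by means as {20a} provides. They do not transfer directly to the medians named in the outcome table. The outcomes that benefit are exploratory, and the sample size of 488 is unaffected.

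**What to change.** In {20a}, or in the statistical analysis plan before data lock:

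- For the duration outcomes (14 and 15), adjust the mean-difference models for parity and cervical dilation (cm, linear) at the last recorded examination before randomisation. Optionally do the same for the caesarean outcomes (1–3).
- For chorioamnionitis, keep the parity-adjusted model as primary. Add dilation only in a prespecified sensitivity analysis, given about 29 expected events.
- State that the no-imputation rule concerns outcomes. A missing baseline dilation is then filled with the overall mean, both arms together, so that no participant is dropped.

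The cost is one field extracted from the chart and a few lines of text. It is better settled now: Methods for additional analyses {20b} allows further analyses to be discussed as the trial data are reviewed, and a covariate added at that stage could look chosen from the data.
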